***3) To examine the role of visuo-cognition in gait in PD***

SEM will be used to assess an
*a priori* hypothesised model of visuo-cognition in gait in PD
^82^. This model will examine the inter-relationships between cognition, visual function, visual sampling (saccade frequency) and gait in PD. SEM is an ideal statistical method for assessing
*a priori* hypotheses, as it allows for hypothesised interactions between variables to be represented within the model. SEM combines ANOVA, correlation, path analysis, factor analysis and regression, and provides direct and indirect relationships between variables, which are not provided by regression analysis
^83^. Direct effects are those where a single path connects one variable to another. Indirect effects are those where the effect of one variable on another goes through a third variable (i.e. more than one path connects two variables)
^84^.

SEM analysis will be conducted using current industry recommendations
^85–
89^. Four steps will be undertaken:
1) Four latent variables will be created (i.e. cognition, visual function, visual sampling and gait) using the same observed variables (e.g. visual acuity) as within the multiple regression analysis.2) Poor latent variable representations will be removed (i.e. observed variables that do not meet a standardised factor loading of ≥0.70 will be removed for each latent variable
^89,
90^).3) Any observed variable with a standardised factor loading of ≥1.00 will be used in place of the latent variable to avoid overfitting
^89^.4) Model trimming and effect calculation; non-significant associations (connection arrows/paths) will be removed, and direct and indirect effects calculated (i.e. for indirect effects coefficients for each path will be multiplied
^91^).

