***1) To examine the independent roles of cognition and vision in gait in PD***

Associations between cognition, visual functions and gait characteristics will initially be made using Pearson correlations, which will be followed by structural equation modelling (SEM) (detailed below).

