***2) To examine the interaction between cognitive and visual functions (termed visuo-cognition)***

Visual sampling (saccade frequency) is an online behavioural measure of visuo-cognition due to its known relationship with cognitive and visual functions
^82^. To analyse visual sampling during gait, a series of mixed analysis of variance (ANOVA) will be used with effect of PD (PD and control) as between participant factor and attention (single task, dual task) and environment (Straight walk, Door, Turn) as within group factors. Pearson’s correlations will be used to test the strength and direction of the relationships between clinical, gait and saccade frequency outcomes. Gait characteristics will also be assessed with the same mixed ANOVA method.

To test the effect of visual cueing on visual sampling and gait; a mixed ANOVA will be used with group (PD and control), visual cue (no cue and cue) and attention (single task, dual task). Comparison with and without a visual cue will also be made via the same mixed ANOVA for the various gait characteristics, while controlling for the influence height.

Associations between cognitive and visual functions will be made using Pearson correlations. Cognitive and visual function contribution to visual sampling will be assessed using multiple regression analysis, while controlling for demographic factors (age, motor severity, depression, global cognition). This will be performed in several steps; Step 1: Demographics, Step 2: Cognition (attention, executive function, visuo-spatial ability, working memory), Step 3: Visual functions (visual acuity, contrast sensitivity), and Step 4: Visuo-cognition (combination of all of the variables in the above steps).

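### No stated analysis linking cognition or vision to gait adjusts for age, although the regression of visual sampling does, so shared ageing can feed the Aim 1 correlations and the SEM paths

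*Protocol article*

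**What the plan says.** All places are in the Protocol article, under Further analysis unless another section is named.

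- **Aim 1** (roles of cognition and vision in gait): associations "will initially be made using Pearson correlations, which will be followed by structural equation modelling (SEM) (detailed below". No adjustment is mentioned.
- **Aim 2** (visuo-cognition): the multiple regression has visual sampling as its outcome and is run "while controlling for demographic factors (age, motor severity, depression, global cognition").
- **Aim 2, cue ANOVA**: gait is compared with and without the visual cue "while controlling for the influence height". This is the only covariate named for any gait analysis.
- **Aim 3** (visuo-cognition in gait): the SEM alone. Its scope is stated as follows: "This model will examine the inter-relationships between cognition, visual function, visual sampling (saccade frequency) and gait in PD". Each of these four constructs becomes a latent variable, and the indicators are chosen by "using the same observed variables (e.g. visual acuity) as within the multiple regression analysis". Paths are then selected by significance: "non-significant associations (connection arrows/paths) will be removed, and direct and indirect effects calculated". An indirect effect is the product of its path coefficients.
- **Discussion**: the results are expected to settle whether gait impairment in PD is influenced by basic visual function, by cognition, or by both.

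**The concern.** Age is a plausible common cause of poorer cognition, poorer vision, altered eye movements and poorer gait. The plan accepts this for visual sampling, since age and motor severity are in the first block of that regression. The same precaution is not stated for gait, which is the outcome in Aims 1 and 3.

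Both factors vary in the sample. Table 1 sets a lower age limit of 50 and no upper limit. Table 3 gives an age SD of 7.60 years in the PD group and Hoehn and Yahr stages I, II and III in 21, 33 and 6 people.

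At stake is the interpretation promised in the Discussion. A link between vision and gait could partly reflect older participants having both poorer vision and poorer gait. Because paths are kept on significance and then multiplied, a path produced by shared ageing would also enter the reported indirect effects.

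**Working it through.** The article gives no figure on this point, so there is nothing to reproduce. The check asks how often a null association would appear significant if age were the only link.

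**Inputs from the article:** n=60 (PD group, taken as the population for Aims 1 and 3, whose titles refer to gait in PD); two-sided 0.05 (Analysis common to all studies).

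**Assumed:** age has the same correlation *a* with each construct, and the constructs are otherwise unrelated. The article gives no value for *a*; the main range is 0.3 to 0.5.

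**Step 1. Induced correlation.** r = a², that is 0.09, 0.16 and 0.25 for a = 0.3, 0.4 and 0.5. The critical |r| at n=60 is 0.254, which a² reaches when a is about 0.50.

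**Step 2. Pearson correlation (Aim 1).** By Fisher's z, the test statistic is centred at atanh(r) × √57, where 57 = 60 − 3:
- r = 0.09: 0.0902 × 7.55 = 0.68; P(significant) about 10%
- r = 0.16: 0.1614 × 7.55 = 1.22; about 23%
- r = 0.25: 0.2554 × 7.55 = 1.93; about 49%

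Simulation (10,000 data sets per setting) gives 10%, 22% and 49%.

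**Step 3. Path to gait (SEM).** Here the other two constructs are also in the model and absorb part of the age effect. With equal correlations, the partial correlation given two others is r/(1 + 2r):
- 0.09/1.18 = 0.076
- 0.16/1.32 = 0.121
- 0.25/1.50 = 0.167

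With √55 (60 − 3 − 2) in place of √57, these give about 9%, 15% and 24%. Simulated least-squares paths (3,000 data sets per setting) give 9%, 15% and 25%.

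**Step 4. The same tests with age included (simulated).**

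| Assumed a | Pearson | Age-partial | Path to gait | Path, age included |
|---|---|---|---|---|
| 0.3 | 10% | 4.8% | 9% | 4.9% |
| 0.4 | 22% | 5.0% | 15% | 5.5% |
| 0.5 | 49% | 5.0% | 25% | 4.6% |

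**Range.** At a = 0.2 the Pearson rate is 6%, hardly above nominal. At a = 0.7 it is 98%, and the path rate is 48%.

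**Limit of the check.** The path figures use observed scores and least squares, not a fitted latent-variable model. They show direction and rough size only.

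**The case against.** **The SEM may contain covariates.** Creating four latent variables does not exclude observed exogenous variables, and the a priori model comes from a cited source that is not shown. A reader might infer that the plan shuts age out of the SEM; the text does not support that. What can be said is that the article names covariates where it uses them, sets out the SEM in four steps, and names none there.

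**The regression variables may carry age in.** The SEM reuses the regression's observed variables, and that regression includes age and motor severity. But the sentence concerns building the four latent variables, and age is not a natural indicator of any of them. Making it an indicator would not adjust for it either. The wording is ambiguous, which is itself a reason to clarify it.

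**The regression and the SEM answer different questions.** This stands. One predicts visual sampling and the other models gait, so they do not contradict each other. The point is only that the precaution taken for one outcome is not stated for the other.

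**Independent roles means each function taken separately.** The Aims contrast independent roles with interaction, so this reading is fair. The point does not depend on Aim 1 promising independence from age.

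**The study is exploratory and the age correlations are assumed.** Both are true, and both limit the weight of the point. At 0.3 the effect on an SEM path is slight (9% against 5%).

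**Conclusion.** The point holds. As described, the Aim 1 correlations and the SEM name no age or severity covariate, so shared ageing can contribute to the cognition, vision, sampling and gait associations and to which paths are retained. Following the text as written would leave the Discussion's question about what influences gait open to an age explanation.

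The size is conditional. For assumed age correlations of 0.3, 0.4 and 0.5, false-positive rates are about 10%, 23% and 49% for a Pearson correlation, and about 9%, 15% and 25% for a path to gait. A reader might apply the 49% to a trimmed SEM path. That would be wrong: trimming applies only to the SEM, where the other constructs take up part of the age effect, and the comparable figure is about 25%. Nor does the article show that age does create these paths; it reports no age correlations. These rates rest on n=60, equal age correlations across constructs and no true link between them.

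This is a change that should be made, tempered by the study's exploratory aim.

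**What to change.** - **Aim 1:** report age-adjusted partial correlations beside the Pearson correlations.
- **SEM:** enter age as an observed exogenous variable with paths to the constructs, and state that it is not subject to the trimming rule. If the a priori model already includes age, say so.
- **Sensitivity analysis:** repeat both with motor severity added. It belongs here and not in the main model because it may lie on the pathway to gait, so that adjusting for it could remove part of the effect of interest.

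Age and motor severity are already variables in the planned regression, and the analyses are described in the future tense, so the change is to the wording of the analysis. The real cost is a few more parameters (up to four age paths) in a model fitted to 60 people, with some loss of precision. A path from height to gait is not required, and neither is replacing the latent variables with composite scores.

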**Methods **

Two groups of older adults (≥50 years old) were recruited; non-demented people with PD (n=60) and age-matched controls (n=40). Participants attended one session and a sub-group (n=25) attended two further sessions in order to establish mobile eye-tracker reliability. Participants walked in a gait laboratory under different attentional (single and dual task), environmental (walk straight, through a door and turning), and cueing (no visual cues and visual cues) conditions. Visual sampling was recorded using synchronised mobile eye-tracker and electrooculography systems, and gait was measured using 3D motion analysis.

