## Statistical analysis

### Sample size

This was an exploratory study and therefore few specific previous examples were available to guide estimates for sample size. We have based the estimate (≥40 participants in each group) on our previous work (PD; n=21)
^29^ and other previous similar studies. Similar studies in this research area
^72,
73,
77–
80^ have used small sample sizes (n=2–26) and reported between-group differences, demonstrating that we will be able to see differences between our sizable PD and control groups. It is a general recommendation to include 30 cases per group to be able to carry out basic statistical tests (e.g. between group comparisons)
^81^. This study will inform future power calculations.

Data analysis will follow a predetermined plan:

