### Analysis common to all studies

Statistical analysis will be undertaken using SPSS version 21 (SPPS, Inc. an IBM company). Demographic characteristics and baseline data will be summarized using descriptive statistics, including means, standard deviations, median, minimum, maximum and inter-quartile ranges for continuous or ordinal data and percentages for categorical data. The descriptive statistics will be tabulated and presented graphically for clarity. One-sample Kolmogorov-Smirnov tests will be used to check for normally distributed data. Non-normally distributed continuous distributions will be transformed where appropriate to meet the requirements of parametric tests; otherwise equivalent non-parametric tests will be adopted. Data will also be assessed graphically (such as histograms or scatter plots) for clarity of information. As this is an exploratory study a threshold of
*p* < .05 (two-sided) will guide statistical interpretation. A brief summary of participant demographic and clinical outcomes is provided in
Table 3.

**Table 3. T3:** Brief summary of demographic and clinical features.

		Control (n=40) Mean (SD)	PD (n=60) Mean (SD)	***p***
Demographic	Age (years)	66.93 (10.86)	67.77 (7.60)	.649
	Sex	17M/23F	38M/22F	**.041** †
	Education (years)	14.80 (3.03)	13.28 (3.61)	**.031 ***
	Depression scale (GDS-15)	0.70 (0.88)	2.80 (2.77)	**.000 ***
	Falls efficacy scale (FES-I)	18.98 (4.15)	25.48 (8.99)	**.000 ***
Clinical	Hoehn and Yahr stage (H&Y)	-	I (21)/II (33)/III (6)	-
	Disease duration (months)	-	75.38 (75.50)	-
	UPDRS part III	-	37.13 (13.84)	-
	FOGQ	-	4.33 (7.21)	-
	LED	-	629.49 (412.82)	-

*independent t-test significance level p<.05, † = X², LED = levodopa equivalent dose, FOGQ = freezing of gait questionnaire and UPDRS III = unified Parkinson’s disease rating scale (motor subsection)

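### The SEM is presented as assessing an a priori model, but its effects are calculated after non-significant paths are deleted on the same data, which distorts the direct and indirect effects that get reported

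*Protocol article*

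**What the plan says.** Under Further analysis, aim 3, the protocol article uses SEM to assess an a priori "hypothesised model of visuo-cognition in gait in PD", linking cognition, visual function, visual sampling (saccade frequency) and gait. It adds that "SEM is an ideal statistical method for assessing" a priori hypotheses.

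Four steps follow. Step 2 drops indicators by their loading in the data: "observed variables that do not meet a standardised factor loading of ≥0.70 will be removed for each latent variable". Step 4 is headed as model trimming: "non-significant associations (connection arrows/paths) will be removed, and direct and indirect effects calculated". On the estimator it says that "for indirect effects coefficients for each path will be multiplied".

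Aim 1 also leads into this SEM after the initial correlations. The Analysis common to all studies section sets a threshold of p "< .05 (two-sided) will guide statistical interpretation". The Sample size section calls the study exploratory. No holdout sample or validation step is described.

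**The concern.** A model whose paths are deleted by significance, and whose effects are then calculated in the same sample, is no longer the model fixed in advance. Three consequences follow.

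- **Real paths disappear.** With about 60 people, non-significance often reflects low power rather than absence of an effect.
- **Surviving effects are too large.** A product of two coefficients that each had to reach significance is selected upwards.
- **A deleted direct path is partly absorbed.** Its effect is re-expressed through saccade frequency.

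This matters because the SEM answers aim 3 and contributes to aim 1. The Discussion expects the study to settle whether visual function, cognition or both influence gait in PD. That is a question about which paths exist, and under step 4 a low-power deletion rule largely decides it.

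**Working it through.** The article states no path values and no power figure for the SEM, so there is no published figure to reproduce. The check asks what the stated rule does under assumed values.

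**Inputs**
- n = 60: the PD group. This is inferred because the model concerns gait in PD; the SEM sample is not stated. n = 100 (all participants) is the alternative.
- Deletion at p ≥ .05: inferred from the general threshold.
- Assumed standardised paths: *a* (cognition to saccade frequency), *b* (saccade frequency to gait), *c′* (direct, cognition to gait). The true indirect effect is *ab*.

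**Step 1: chance of deleting a real direct path** (*a* = *b* = 0.3, *c′* = 0.2)
- Explained variance of gait = *c′*² + *b*² + 2*abc′* = 0.04 + 0.09 + 0.036 = 0.166, so residual variance = 0.834.
- Standard error of *c′* at n = 60 = √[0.834 / (57 × (1 − 0.09))] = √(0.834 / 51.87) = 0.127.
- Expected z = 0.2 / 0.127 = 1.58. Power ≈ Φ(1.58 − 1.96) = 0.35, so the path is deleted in about **65%** of samples.
- At n = 100, standard error = √(0.834 / 88.27) = 0.097, z = 2.06, and deletion is about **46%**.

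Simulation gave 65 to 66% at n = 60 and 47% at n = 100.

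**Step 2: indirect effects that survive.** Two observed-variable simulations were used.
- A: one predictor, 6,000 samples per setting. The direct path is dropped if p ≥ .05, and the indirect effect is kept only if both legs have p < .05.
- B: cognition and vision as predictors (correlation 0.3, vision paths 0.2), 5,000 samples per setting, backward deletion at p ≥ .05 with refitting.

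Results at n = 60:

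| *a*, *b*, *c′* | True *ab* | Untrimmed mean (B) | Surviving mean, A | Surviving mean, B | Survives (B) | All samples, deleted = 0 (B) |
|---|---|---|---|---|---|---|
| .4, .4, .2 | 0.160 | 0.159 | 0.191–0.193 | 0.207 | 85% | 0.176 |
| .3, .3, .2 | 0.090 | 0.091 | 0.146–0.152 | 0.155 | 53% | 0.083 |
| .3, .2, .2 | 0.060 | 0.061 | 0.130 | 0.142 | 33% | 0.046 |
| .2, .2, .2 | 0.040 | 0.040 | – | 0.126 | 18% | 0.022 |

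- Legs of 0.4: 0.191/0.160 = 1.19 to 0.207/0.160 = 1.29.
- Legs of 0.3: 0.146/0.090 = 1.62 to 0.155/0.090 = 1.72.
- Legs of 0.2: 0.126/0.040 = 3.15.
- At n = 100 with legs of 0.3, the surviving mean is 0.110 (A) or 0.117 (B) against 0.090, an excess of 22 to 30%.

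**Step 3: false appearance of full mediation.** With legs of 0.3 and *c′* = 0.2, the real direct path was missing in 75 to 76% (A) or 69% (B) of samples where the indirect effect survived. Over all samples in A this is about 0.49 × 0.75 = 37%.

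**Step 4: where the excess comes from.** In A, among samples where mediation survived, the untrimmed estimate already averaged 0.134 and the trimmed one 0.148.
- Selection on significance accounts for (0.134 − 0.090) / (0.148 − 0.090) = 0.044/0.058 = 76% of the excess.
- Absorption of the direct path accounts for the rest. Always deleting *c′* would move *b* to 0.3 + 0.3 × 0.2 = 0.36 and the product to 0.3 × 0.36 = 0.108. That is 20% above 0.090, so absorption alone cannot explain 60 to 70%.

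**Step 5: no true mediation.** With *a* = 0.5, *b* = 0 and *c′* = 0.2 or 0.3, a mediated path was reported in roughly 8 to 13% of samples across runs. With *a* = 0.3 and *b* = 0 it was about 6%.

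**The case against.** The strongest reply has four parts.

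- **Direction.** A reader might infer that trimming always pushes results towards the study's own hypothesis. It does not. The rule also deletes the hypothesised indirect paths. With legs of 0.3 they survive in only about half of samples, and the all-sample mean is 0.071 to 0.083 against 0.090. It rises above the truth only with strong legs (0.176 against 0.160). This part stands, and the point is limited accordingly.
- **Openness.** A reader might also infer that a searched model is being passed off as fixed in advance. The article names trimming as a step and states the rule beforehand. It does not speak of full mediation and does not say that a deleted path means no effect. What remains is the conflict between the a priori description and a calculation made after selection.
- **Unknowns.** The hypothesised model is in a cited source, so its direct paths cannot be seen. The SEM sample and deletion threshold are inferred, and every magnitude rests on assumed effects. This stands as a limit on size, not on the mechanism.
- **Status.** The study is labelled exploratory: "This was an exploratory study and therefore few specific previous examples were available to guide estimates for sample size". Its primary outcome, saccade frequency, is analysed by mixed ANOVA, which trimming does not touch. Interval methods may be left to a fuller plan. This lowers the severity, but the deletion rule itself is fixed in the text and is not an omitted detail.

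**Conclusion.** The concern holds as a should-fix point. Followed as written, step 4 yields direct and indirect effects from a model selected on the same data, so they do not assess the a priori model.

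At about n = 60, a real direct path of 0.2 is lost in about 65% of samples, and partial mediation then often appears as full. Surviving indirect effects are too large by about 20 to 30% (legs of 0.4) or 60 to 70% (legs of 0.3), and by more for weaker legs. The distortion is smaller but present at n = 100. It is mainly selection on significance, with a smaller share from absorption of the deleted direct path.

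These sizes rest on assumed path values and observed-variable models. The further selection by loadings in steps 2 and 3 was not simulated. A uniform bias towards mediation is not supported, and neither is a more severe rating for a study that declares itself exploratory.

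**What to change.** Make the untrimmed hypothesised model the main SEM result. Report every path and all direct and indirect effects with bootstrap 95% confidence intervals, whether or not they are significant. Reporting all of them is essential: in simulation A with legs of 0.3, highlighting only the significant indirect effects of the full model still gave a mean of 0.141 against 0.090, and intervals alone do not cure that.

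Show any trimmed model only as a labelled exploratory description. Do not read a deleted path as absence of effect when answering the Discussion's question about vision, cognition or both. State the SEM sample and the deletion threshold.

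The change needs revised analysis wording and bootstrap runs, with no new data. The downside is wider intervals and a less tidy summary.
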